## Abstract

**Background:**

Globally, 21 million children do not receive the measles vaccine each year. With high levels of mobile phone access and ownership, opportunities exist to leverage mobile health technologies to generate demand for immunization.

**Objective:**

The aim of the Mobile and Scalable Innovations for Measles Immunization trial is to determine if text message (short message service, SMS) reminders, either with or without mobile phone–based incentives, can improve measles immunization coverage and timeliness in rural western Kenya.

**Methods:**

This is a 3-arm, parallel, randomized controlled trial (RCT). Using simple randomization, caregivers in Siaya County, Kenya, will be randomized and evenly allocated to 1 of 3 study arms: (1) control, (2) SMS reminders only, and (3) SMS reminders plus a 150 Kenyan Shilling (KES) incentive. Participants assigned to the SMS group will be sent SMS reminders 3 days before and on the day before the measles immunization visit scheduled for when the child is 9 months of age. Participants in the incentive arm will, in addition to SMS reminders as above, be sent an unconditional 150 KES mobile-money incentive to their mobile phone 3 days before the child becomes 9 months of age. Children will be followed up to the age of 12 months to assess the primary outcome, a measles vaccination by 10 months of age. Log-binomial regressions will be used to calculate relative risks.

**Results:**

Enrollment was completed in March 2017. We enrolled 537 caregivers and their infants into the following groups: control (n=179), SMS reminders only (n=179), and SMS reminders plus 150 KES (n=179). Results will be made publicly available in 2020.

**Conclusions:**

Few RCTs have examined the effect of text message reminders to improve measles immunization coverage. This is the first study to assess the effect of SMS reminders with and without unconditionally provided mobile-money incentives to improve measles immunization coverage.

**Trial Registration:**

ClinicalTrials.gov NCT02904642; https://clinicaltrials.gov/ct2/show/NCT02904642 (Archived by WebCite® at http://www.webcitation.org/78r7AzD2X).

**International Registered Report Identifier (IRRID):**

RR1-10.2196/13221

## Introduction

### Background

In 2017, 20.8 million age-eligible children worldwide did not receive measles-containing vaccine [1]. Measles is a highly contagious virus, which is evident from measles outbreaks occurring in populations comprising as little as 10% susceptible, or immunologically unprotected, individuals [2]. Given that every year immunization programs are estimated to save over 3 million lives globally [3], innovative interventions that are easily scaled and that target hard-to-reach and underimmunized populations are needed.

Mobile phone technologies and tools, broadly referred to as mobile health, have been used successfully for a variety of public health problems [4,5] and to strengthen and improve health systems [6,7]. The Classification of Digital Health Interventions, released by the World Health Organization in 2018, categorizes digital health interventions by the health systems challenges they address [8]. As mobile phone ownership and access levels continue to rise in lower income countries [9], digital health solutions that address demand-side deficiencies in immunization services become more realistic.

Short message service (SMS), or *text message*, reminders and incentives are 2 of the more common interventions that have been used to generate demand for immunization services [10,11]. Text message reminders have been shown to modestly improve immunization uptake in studies in the United States and other high-income countries [12]; although their evidence to improve uptake in low- and middle-income countries (LMICs) is limited. [13].

With regard to incentives, at least 4 studies have evaluated the impact of small monetary and nonmonetary incentives, such as coupons and food, on vaccination in LMICs. Studies in India [14], Kenya [15-17], and Pakistan [18] found that monetary and nonmonetary incentives have the potential to improve vaccination coverage and also suggest that incentive-based interventions have the potential to affect hard-to-reach populations. Moreover, all of the identified studies provided a conditional incentive, where the caregiver was only given the incentive if the child was vaccinated. To our knowledge, no studies have provided unconditional incentives for vaccination.

This study builds on the success of the recently completed Mobile Solutions for Immunization (M-SIMU) cluster randomized controlled trial (RCT). The M-SIMU trial found that providing a 200 Kenyan Shilling (KES) mobile-money incentive, or approximately US $2.50 at the time of the study, conditionally to caregivers who vaccinated their child within 2 weeks of the Expanded Program on Immunizations (EPI) due date significantly improved the proportion of fully immunized children and measles vaccination coverage measured at 12 months [15,19]. A conditional incentive approach may be difficult to scale because it requires staff at the clinic to document immunization and to calculate whether the immunization was received in time. Additionally, unconditional incentives may be more effective at increasing the intended health outcome if the transferred money is used to offset incurred travel costs, rather than receiving the money after visiting the health facility, as in a conditional approach.

### Objective

To counter these logistical and implementation challenges and to facilitate their scalability, the Mobile and Scalable Innovations for Measles Immunizations (M-SIMI) RCT seeks to evaluate the impact of providing rural Kenyan caregivers SMS reminders and unconditional monetary incentives on measles immunization coverage at 10 months of age.

## Methods

### Study Design

The M-SIMI study is an individually randomized, parallel, controlled trial (Figure 1). Caregivers will be randomized into 1 of 3 study arms using a 1:1:1 allocation ratio. The study arms include (1) control, (2) text message reminders only (SMS only), and (3) text message reminders plus a 150 KES incentive (SMS plus 150 KES); where 100 KES=US $1 as of June 2016. Participants randomized to the intervention arms will be sent 2 SMS reminders—3 days and 1 day before measles immunization visits scheduled at 9 months of age. Incentives will be unconditionally sent to the participant’s mobile phone 3 days before the measles vaccination due date at 9 months of age. The trial is registered with ClinicalTrials.gov (NCT02904642; September 2016).

### Setting and Participants

The M-SIMI study will take place within the boundaries of the Kenya Medical Research Institute (KEMRI) and the Centers for Disease Control and Prevention (CDC) Health and Demographic Surveillance System (HDSS) in Siaya County, Kenya. The rural study site has high levels of malaria, tuberculosis, and HIV transmission [20]; the majority of residents are subsistence farmers; and approximately 50% of caregivers own a mobile phone [21]. Data from the control arm of our previously conducted RCT found that 98% and 51% of children received pentavalent and measles vaccination by the age of 12 months, respectively [15].

The HDSS has served as a platform for numerous studies, including the M-SIMU trial, which provided text message reminders and conditional mobile-money incentives for pentavalent and measles vaccinations [15]. Potential caregivers and their children will be identified by community health workers (CHWs). CHWs are a component of Kenya’s national community health strategy and typically have a catchment area of 1 village, where the CHW visits each household at least once a month to provide minimal health services and education. Community interviewers (CIs) hired by the project will approach CHW-identified caregivers to describe the study and screen caregivers for their eligibility on the following criteria (see Textbox 1).

Caregivers will be enrolled into the study independent of mobile phone ownership. Caregivers only need to have access to a mobile phone, where access will be defined by the participant. If a caregiver cannot identify an accessible mobile phone, CIs will relay text message reminders and incentives to the participant. Caregivers will neither be provided a mobile phone nor airtime.

**Figure 1 figure1:**
[figure not shown]
Consolidated Standards of Reporting Trials diagram of study design. SMS: short message service; KES: Kenyan Shilling.

The Mobile and Scalable Innovations for Measles Immunizations screening criteria.Inclusion criteria:Caregiver of infant aged 6 to 8 months at the time of enrollmentSelf-reported resident of one of the study villagesWilling to sign informed consent for the studyExclusion criteria:Child of enrolled caregiver has already received 1 dose of measles vaccine, not including any supplemental measles vaccinesCaregiver plans to move away in the next 6 months

### Procedures

#### Enrollment

During their monthly visit, CHWs will identify households with children aged 6 to 8 months. CHWs will approach caregivers of age-eligible children, provide a brief explanation of the study, and answer any questions the caregiver might have. The CHWs will call the field supervisor to notify the study team that they have identified a child aged 6 to 8 months. The field supervisor will then assign a CI to visit the child’s compound to explain the trial and screen the caregiver for the eligibility criteria as described above.

Eligible caregivers will be required to provide written informed consent to the CI. Upon obtaining written informed consent, the CI will send an enrollment SMS to the RapidSMS server, a free and open-source platform. The enrollment SMS is structured and requires the CI to enter the study identification number, the phone number that can be used to receive text message reminders, the child’s date of birth, the preferred language to receive reminders, the child’s first and last name, and the study arm. If the CI sends an incorrectly formatted SMS, he or she will receive an error SMS, which asks the CI to correct the SMS. The RapidSMS server will then send a personalized text message to the newly enrolled caregiver that welcomes him or her to the study (Table 1). The CI will confirm receipt of the enrollment SMS.

#### Control Arm

Aside from the welcome text message received at the enrollment visit, no additional text messages or incentives will be sent to caregivers randomized to the control arm.

#### Intervention Arms

The interventions, text message reminders, and unconditional incentives are designed to motivate caregivers and increase demand for measles vaccination. At enrollment, participants who were randomized to an intervention arm will be told to expect 2 text message reminders for measles vaccine; first, at 3 days before and, second, on the day before the scheduled visit for measles vaccination at 9 months of age. At most, enrolled caregivers will receive 3 text messages (2 for the measles vaccine and 1 for welcoming the caregiver to the study). Text messages will be sent in English, Kiswahili, or Dholuo language, according to the caregiver’s preference.

Caregivers randomized to the incentive study arm will, in addition to being told about SMS reminders as described above, be informed of the measles vaccine due date and that the project will send a 150 KES incentive 3 days before the child turns 9 months (ie, sent on the same day as the first SMS reminder). Caregivers will receive this one-time mobile-money incentive unconditionally. The incentive is intended to subsidize the cost of transportation to the health facility. The transaction costs associated with mobile-money transactions will be borne by the study such that caregivers will receive the full 150 KES. The incentive amount was informed by results of the M-SIMU trial [15].

### Randomization

Caregivers will be evenly randomized (1:1:1) to 1 of 3 study arms. A computer will randomly allocate the study arm to 537 unique study identification numbers. The study identification numbers will be divided into 5 groups (for each of the 5 CIs who will enroll caregivers) and labeled A to E. Each group will contain 109 study identification numbers, labeled 1 to 109. For example, group A will have study IDs labeled 001A through 109A, group B will have study IDs labeled 001B through 109B, etc. The allocation code will be saved on the data manager’s computer. The allocation will be printed on a small card and placed in an opaque envelope by the data analyst. The envelopes will be sealed and stamped to ensure that they cannot be tampered with. Biweekly, the study coordinator will deliver the sealed envelopes to the field supervisor who will then distribute them to the CIs.

CHWs will identify eligible caregiver-infant pairs and place a phone call to the field supervisor to provide information on the location of the child. The field supervisor will notify CIs who will then approach caregivers of age-eligible children to conduct a screening for further eligibility requirements and to obtain informed consent. If the caregiver is eligible for the study and decides to participate, the CI will open the envelope containing the study arm and read the appropriate informed consent form to the caregiver.

**Table 1 table1:** Content of text messages sent to caregivers’ mobile phones.

Message type	Message timing	Arm 1: control	Arm 2: SMS^a^ only	Arm 3: SMS+150 Kenyan Shilling
Enrollment message	Enrollment	Thank you for enrolling Baby <BABY’S FIRST NAME> in M-SIMI^b^ study. The greatest wealth is health. This study is sponsored by KEMRI^c^.	Thank you for enrolling your child in the KEMRI M-SIMI study. You will get SMS reminders for Baby <BABY’S FIRST NAME>’s measles vaccination. The greatest wealth is health.	Thank you for enrolling your child in the KEMRI M-SIMI study. You will get SMS reminders for Baby <BABY’S FIRST NAME>’s measles vaccination. The greatest wealth is health.
3 day reminder message	Date of birth + 9 months – 3 days	No message	Tell Mama <BABY’S FIRST NAME> that Measles vaccine is due this week. Most Gem babies get vaccinated, be one of them!	Tell Mama <BABY’S FIRST NAME> that Measles vaccine is due this week. We are sending 150ksh to assist with travel. Most Gem babies get vaccinated, be one of them!
1 day reminder message	Date of birth + 9 months – 1 day	No message	Tell Mama <Baby Fname> that Measles vaccine is due this week. Go to the clinic if you haven’t already. Vaccines save Kenyan babies lives.	Tell Mama <Baby Fname> that Measles vaccine is due this week. Go to the clinic if you haven’t already. Vaccines save Kenyan babies lives.

^a^SMS: short message service.

^b^M-SIMI: Mobile and Scalable Innovations for Measles Immunizations.

^c^KEMRI: Kenya Medical Research Institute.

Due to the nature of the intervention, participants will not be blinded to the study arm. Additionally, because this trial is conducted to mimic circumstances of what a scaled reminder or travel subsidy program would look like, participants will be told which study arm they have been assigned to at enrollment. As an example, in a scaled program, caregivers would know that they would receive an incentive when their child reached the age of 9 months. Trained interviewers will not be blinded to study arm allocation because of the nature of the trial.

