### Data Analysis

The analysis and reporting of results will be conducted in accordance with the Consolidated Standards of Reporting Trials [22]. A blinded statistician will conduct analyses for primary and secondary outcomes. The primary analyses will be conducted with intention-to-treat principles. The primary outcome, measles immunization at 10 months of age, will be defined as a binary variable. Log-binomial regressions to calculate risk ratios for achieving the primary outcome will be calculated for the intervention arms as compared with the control arm. As a secondary analysis of the primary outcome, time-to-immunization curves will be constructed using the Kaplan-Meier method, and study arms will be compared using the Cox model. The 25th, 50th, and 75th percentiles for time to measles immunization will also be calculated by the study arm. Effect estimates will be presented in whole and stratified on mobile phone ownership and clinic proximity. Mobile phone ownership will be defined as a binary variable (*owns a mobile phone* or *doesn’t own a mobile phone*). Additional stratified estimates will be presented based on calculated risk factors for not receiving measles vaccine in control arm infants. Adjusted analyses will be conducted if our randomization produced imbalanced sociodemographic characteristics by the study arm. A per-protocol analysis of primary and secondary outcomes will also be conducted. Per-protocol delivery of the interventions will be defined as caregivers who were sent 2 text message reminders for measles vaccination in the 2 intervention arms and as caregivers who were sent an incentive in the third study arm.

Socioeconomic quintile scores will be calculated using a multiple correspondence analysis of household assets, livestock owned, water source, type of cooking fuel used, and occupation [23]. In villages where HDSS and CHWs are active, we will conduct a sensitivity and specificity analysis of our CHW approach to identify age-eligible children. The HDSS database, which relies on village reporters to enumerate the population, will be used as the gold standard. We will compare the costs of a CHW versus HDSS approach of identifying eligible children. An alpha of .05 will be assumed for all statistical tests of significance.

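### The allocation envelope is opened before the consent form is read and signed, so an analysis of enrolled caregivers only is exposed to refusals that differ by arm

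*Protocol article*

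**What the plan says.** All references are to the protocol article.

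- **Randomization, allocation.** "A computer will randomly allocate the study arm to 537 unique study identification numbers". The cards are placed in opaque, sealed, stamped envelopes. The same paragraph describes five interviewer groups of 109 numbers each.
- **Randomization, visit.** The community interviewer visits "to conduct a screening for further eligibility requirements and to obtain informed consent". The envelope step carries a condition: "If the caregiver is eligible for the study and decides to participate". Once that condition is met, the article says that "the CI will open the envelope containing the study arm and read the appropriate informed consent form to the caregiver".
- **Enrollment.** "Upon obtaining written informed consent, the CI will send an enrollment SMS to the RapidSMS server". That message carries the study arm.
- **Randomization, blinding.** To mimic a scaled programme, "participants will be told which study arm they have been assigned to at enrollment".
- **Data Analysis.** "The primary analyses will be conducted with intention-to-treat principles". Also: "Adjusted analyses will be conducted if our randomization produced imbalanced sociodemographic characteristics by the study arm".
- **Results.** 179 caregivers were enrolled in each of the three arms, and enrolment ended in March 2017.

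**The concern.** Sealed envelopes protect the allocation only until they are opened. Here the opening comes before written consent, and written consent is what admits a caregiver to the trial. Between the two steps, both the caregiver and the interviewer know the arm.

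The arms differ in appeal: the control arm gets a welcome message only, while the incentive arm gets two reminders and 150 KES without conditions. A caregiver who was willing in principle may withdraw on learning that she is a control, and one offered money has a reason to stay. If those who withdraw differ in their inclination to vaccinate and are dropped, the enrolled arms are no longer comparable.

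The described safeguards do not close this route:

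- The enrolment message follows consent, so it would not record a caregiver who declined.
- Adjustment is triggered by imbalance in sociodemographic characteristics and would not reliably remove selection on motivation.
- The Limitations section discusses unblinded outcome collection but not this step.

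**Working it through.** **1. Order of steps.** Taking Randomization and Enrollment together, the sequence is: screening; provisional decision to take part; envelope opened; consent form read; written consent; enrolment message. The form cannot be signed before it is read, so written consent follows disclosure. The reason given for openness covers telling caregivers their arm at enrolment. It does not require telling them before they sign.

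**2. The plan's own sample size.** Inputs (Sample Size): 70% v 85%, alpha .05, power 0.80, 25% loss. Two-sided, without continuity correction:

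n = [1.96·√(2 × 0.775 × 0.225) + 0.8416·√(0.70 × 0.30 + 0.85 × 0.15)]² / 0.15² = 120.5, i.e. 121.

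With continuity correction: (120.5/4)·[1 + √(1 + 4/(120.5 × 0.15))]² = 133.5, i.e. 134. Then 134/0.75 = 178.7, i.e. 179, and 3 × 179 = 537. The stated figures reproduce. The named reasons for loss do not include refusal after allocation.

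**3. Size of a possible bias (assumed refusal figures, none from the document).** Let r be the share of controls who decline after opening and q the coverage they would have had. Assume no refusals in the comparison arm. Coverage among enrolled controls is (0.70 − r·q)/(1 − r).

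| r | q | Enrolled control coverage | Shift (points) |
|---|---|---|---|
| 0 | any | 70.0% | 0 |
| 10% | 0.5 | 0.65/0.90 = 72.2% | +2.2 |
| 10% | 0.4 | 0.66/0.90 = 73.3% | +3.3 |
| 12% | 0.4 | 0.652/0.88 = 74.1% | +4.1 |
| 10% | 0.9 | 0.61/0.90 = 67.8% | −2.2 |

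The direction depends on who declines. With 134 analysed per arm and 85% in the intervention arm, power without continuity correction is 0.84 at no refusal and 0.73 for r = 10%, q = 0.5. For r = 12%, q = 0.4 and no true effect, a two-sided 5% test rejects 11.6% of the time, mostly in the direction of apparent harm.

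**4. What the counts can tell.** Under independent simple randomisation of 537 caregivers, exactly 179/179/179 has probability 537!/(179!³ · 3⁵³⁷) = 0.0015. A fixed list of 537 cards used to the end is more plausible. That fits no refusals after opening, but also replaced or re-used envelopes. In addition, 5 × 109 = 545 labelled numbers, 8 more than 537, so spare numbers are a further possibility.

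Suppose those 8 were real envelopes, all used up by refusing controls, with none re-used. Then r = 8/(179 + 8) = 4.3%, and the shift is +0.9 points (q = 0.5), +1.3 (q = 0.4) or −0.9 (q = 0.9). If envelopes were re-used, this ceiling does not apply.

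**5. What bounds would look like.** With r = 10% and enrolled control coverage of 72.2%, coverage over all opened control envelopes lies between 0.90 × 72.2% = 65% (refusers unvaccinated) and 65% + 10% = 75% (refusers vaccinated). This contains the assumed true 70%. Against 85% in an arm with no refusals, the difference lies between 10 and 20 points.

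**The case against.** The other side has several good points.

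- **A decision precedes opening.** Screening and a first decision to take part come before the arm is known, so an interviewer cannot select on eligibility by arm. This stands. Only a caregiver who changes her mind is at issue, which probably makes refusals rarer but does not rule them out.
- **The text could mean consent comes first.** The visit is said to include obtaining consent before the envelope is mentioned, and the form might be appropriate to language rather than arm. But the one sentence that gives the order has the form read after opening. Even a form that did not vary by arm would be read with the arm known.
- **No refusals are reported.** This stands. A reader might infer that randomisation has been lost, or that 179 per arm proves either no refusals or re-used envelopes. The document supports neither: bias needs omitted refusals that differ by arm, and the 545 v 537 mismatch leaves other explanations.
- **Baseline answers given with the arm known.** A reader might also infer this, but the article does not place the enrolment survey before or after opening.
- **Detail left to a fuller document.** How refusers are counted commonly sits elsewhere, and its absence is not held against the article. The sequence, however, is stated here.
- **The shift is small and assumed.** Two to three points is less than one standard error of control coverage, √(0.70 × 0.30/134) = 4.0 points. That is fair, but a systematic shift is not captured by the confidence interval.

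**Conclusion.** The concern holds in limited form. As described, allocation is disclosed after a provisional decision but before written consent, and enrolment depends on that consent. An analysis restricted to enrolled caregivers is therefore open to differential refusal after allocation, in either direction. Whether any bias occurred is unknown, and it is zero if nobody declined after opening. If 10% of controls declined, the shift in control coverage would be about 2–3 points either way across the assumed values of q, against a target difference of 15. These refusal rates and coverages are assumptions. Confidence is high in the sequence and low in any size. This should be fixed before results are reported. It is not evidence that the trial's randomisation failed.

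**What to change.** **Design principle.** Take written consent, on one form that covers all three arms, before the envelope is opened. This is too late for this trial but applies to any repeat. Its price is that controls learn of the reminders and the 150 KES.

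**For this trial, enrolment being complete:**

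1. Reconcile every opened envelope with the enrolled IDs, and explain 545 against 537.
2. Report, by arm, the caregivers who declined after opening and any envelope re-used or replaced. If there were none, one sentence closes the point.
3. If there were refusals, add a sensitivity analysis of the primary outcome with every opened allocation in the denominator, counting refusers as unvaccinated and then as vaccinated. If more than one arm is affected, also use opposite settings between arms, since equal settings do not then give the extremes. Caregivers who declined have no outcome data, so they can enter only as counts in this bounding analysis.

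**Cost.** A count from envelope and ID records, provided these were kept, and one extra analysis. The bounds may be somewhat less favourable than the main estimate. If the records were not kept, that should be stated as a limitation.
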